#### Neuroinflammatory-Related Complications

After 30 days postsurgery, patient medical dossiers will be consulted, and any incidence of delirium and POCD will be recorded.

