### Treatment Allocation

This study will take the form of an on-off NCT [26]. An on-off NCT takes into account real-world setting limitations of certain intervention types and allocates participant inclusion by alternation. The main reason for this is that MiMiC is a well-researched intervention, whose practical implementation is not suited for randomly selected participants to not participate. On the one hand, musicians will visit the nurses’ station and play music in various rooms around the ward; thus, it is not possible to prevent participants who may be allocated non-MiMiC treatment from hearing the live music. On the other hand, a central tenet of the MiMiC intervention is inclusion and participation, thus “rejecting” patients who would want to participate in music they hear on the ward, on the basis of trial group allocation, goes against the spirit of the intervention.

In contrast, the NCT relies on the randomness of who is scheduled for surgery during a given intervention week but does not exclude any patient from the activity being conducted (listening to live or recorded music). Therefore, the treatment schedule (live music intervention, recorded music active control, and standard care control) will be predetermined months in advance, and the patients included will be offered whichever treatment is occurring during their hospital stay. The patients will, however, be asked for their consent before they are informed which treatment will be offered during their surgery recovery. This will attempt to prevent patients who are initially biased for inclusion based on their affinity to music or not.

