#### Blood Marker Analysis

One 10-ml vial of blood will be collected per day resulting in a maximum of 5 vials of blood over 5 days. The first sample must be taken before the first assigned intervention. Blood samples will be collected together with standard care insofar as possible. Serum extracted from blood samples will be processed by the Haemoscan lab and evaluated for the presence of 4 markers associated with neuroinflammation (IL6, NGAL, CRP, and serum TPSO; see “Introduction” section).

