### Secondary Study Parameters

For metrics that are collected on the same schedule as the VAS (EEG alpha power, delta/alpha power ratio, entropy metrics, HR, respiration rate, and blood pressure), the values per participant will be entered into the same *F* test described for the VAS ratings (as well as correlated with other baseline parameters as described in the “Other Parameters” section). For blood marker metrics that have 2 data collection points, a similar RM ANOVA will be conducted, but with 2 as opposed to 4 measures, and a significant interaction between treatment and time point would indicate whether treatment significantly impacted the amount of the neuroinflammatory blood marker. Categorical incidence metrics (delirium and POCD) will be evaluated with a one-way ANOVA to determine whether treatment impacted these neuroinflammatory-related complications. Delirium and signs of delirium will be perceived using the DOSS. The DOSS is a screening instrument for delirium, consisting of 13 items, and will be filled by a registered nurse during hospital admission until discharge. Nurses have frequent contact with the patients and are in a good position to observe behavior changes 24 hours a day when patients are admitted. The DOSS is already part of a routine in the surgical wards and all registered nurses are already trained. Likewise, scalar pain medication dosage will be averaged over 24-hour periods per patient and entered into a chi-square test to determine whether the dosage was significantly different across the 3 treatment groups. As this is exploratory and serves to inform future hypothesis-directed testing, we will not correct for multiple comparisons.

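### Delirium is counted over the whole admission with no start at the first session, so episodes that precede any music count as treatment outcomes (minor; secondary, exploratory outcome)

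*Protocol article*

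**What the plan says.** **Delirium.** The Protocol article, Neuroinflammatory-Related Complications, has the dossiers read once 30 days have passed since surgery, when "any incidence of delirium and POCD will be recorded". Secondary Study Parameters adds that the DOSS "will be filled by a registered nurse during hospital admission until discharge". The incidence data then "will be evaluated with a one-way ANOVA to determine whether treatment impacted these neuroinflammatory-related complications".

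**Analgesics.** The same section states: "scalar pain medication dosage will be averaged over 24-hour periods per patient and entered into a chi-square test". It does not say when a 24-hour period begins.

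**Start of treatment.** Treatment Allocation states: "the patients included will be offered whichever treatment is occurring during their hospital stay". Table 1 puts the live, recorded or no-intervention slot at 10:40 to 11 AM. Study Design gives three 5-day treatment periods separated by 7-day washouts.

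**Outcomes that are anchored.** Blood Marker Analysis requires: "The first sample must be taken before the first assigned intervention". Study Design gives pain VAS, heart rate and blood pressure a reading before each session.

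**The concern.** The comparison is meant to show whether treatment changed delirium incidence, but the counting window opens at admission. Treatment starts only at the first session, which will normally follow at least the first night after surgery. An episode in that interval is an event of the arm although no music has been given. The article takes a pre-session reading for the blood markers and vital signs, so the lack of any such separation for delirium is an inconsistency in how outcomes are defined.

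Randomisation would balance such early events in expectation. Here allocation follows the calendar, so balance is plausible but not guaranteed. These comparisons are meant to generate hypotheses for later trials, and a diluted signal could lead the investigators to discard a real effect.

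The analgesic outcome raises a milder form of the same question, because no start is given for its 24-hour periods.

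**Working it through.** **The plan's own figure.** The article gives no figure for delirium or analgesic use. Its only sample-size calculation is for the VAS group-by-time interaction, and it reproduces: λ = f² × N = 0.2318206² × 327 = 17.573; df = (3−1)(4−1) = 6 and (327−3)(4−1) = 972; critical F = 2.1079; power = 0.9008, as in Table 3. That gives the 109 per arm used below. The point does not touch this calculation.

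**Delirium: dilution.** Assumed inputs, none from the article: a share q of control-arm episodes precedes the first session (20% to 60%), and music halves the risk afterwards. With q equal across arms, the counted risk ratio is RR = q + (1 − q) × 0.5.

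- q = 0: 0.50
- q = 0.2: 0.2 + 0.8 × 0.5 = 0.60
- q = 0.4: 0.4 + 0.6 × 0.5 = 0.70
- q = 0.6: 0.6 + 0.4 × 0.5 = 0.80

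**Does restricting the count lose power?** Two-proportion comparison of one music arm with control, 109 per arm, two-sided 0.05, control rates assumed:

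| Control rate | q | Power, all episodes | Power, post-session episodes only |
|---|---|---|---|
| 20% | 0 | 54% | 54% |
| 20% | 0.2 | 36% | 44% |
| 20% | 0.4 | 22% | 34% |
| 20% | 0.6 | 12% | 24% |
| 10% | 0 | 29% | 29% |
| 10% | 0.2 | 19% | 24% |
| 10% | 0.4 | 12% | 19% |
| 10% | 0.6 | 7% | 14% |

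The last column keeps 109 in each denominator. Removing patients already delirious at the first session changes little. At a 20% rate and q = 0.4, 109 × 0.2 × 0.4 = 8.7 patients per arm leave, about 100 remain, and the control rate becomes 0.12/0.92 = 13.0% against 6.5%. The risk ratio is 0.50 and the power is still 34%.

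**Delirium: unequal lags.** Suppose two music arms both halve later risk, but 20% of the episodes expected without music precede the first session in one arm and 60% in the other. Their counted risk ratios against control are 0.60 and 0.80, a ratio of 0.60/0.80 = 0.75 between equally effective arms. With equal lags this ratio is 1.

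**Analgesics, only if periods are calendar days.** Assume even dosing and averaging over treatment days only. The time before 10:40 on the first day is 10.67 h. Its share over d days is 10.67/(24d), and a true 20% reduction appears as 20% × (1 − share).

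- 1 day: share 44%, seen as 11%
- 2 days: 22%, 16%
- 3 days: 15%, 17%
- 5 days: 9%, 18%

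If the periods run from the session, the share is zero and nothing is lost.

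**The case against.** **The analgesic part is silence, not a stated error.** The article never says calendar day. Study Design mentions daily dosage alongside procedures that repeat on each treatment day, and a condensed article may leave the start of the period to a fuller document. This stands. A reader might infer that doses given before any music are certainly counted, but the text does not establish that. It supports only a request to state the start.

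**Several untreated days are not established.** A reader might infer from Treatment Allocation that patients operated on days before a treatment period opens are included. The same section ties allocation to who has surgery scheduled in the week of a given intervention, and Recruitment refers to admissions in planned study weeks. This weakens the long-lag scenario. It does not remove the interval between surgery and the first session.

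**A false difference has no demonstrated cause.** All arms have the same 5-day period and the same clock slots. Postoperative day is recorded, and the post hoc analyses allow continuous baseline parameters as covariates. This also stands: unequal lags are possible under calendar allocation, but nothing in the article shows them.

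**The delirium sizes are assumed, and the outcome is exploratory.** Both are true. Even with no early episodes, the assumed scenarios give at most 54% power, so no counting rule makes this a reliable comparison. This lowers the priority, but the stated delirium window still includes time before treatment.

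**Conclusion.** The point holds for delirium on the stated text: the window opens at admission, every episode in it counts, and the result is read as an effect of treatment. The expected consequence is dilution towards no difference, with a counted risk ratio of 0.60 to 0.80 instead of 0.50. That rests on two assumptions the article does not supply: 20% to 60% of control-arm episodes before the first session, and a halving of later risk. Bias that favours one arm would need a different surgery-to-session lag between arms, and should be treated as a possibility to check.

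For analgesics the finding is only that the start of the 24-hour periods is unstated. Under calendar days and even dosing, a true 20% reduction would appear as about 11% with one treatment day and 18% with five.

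The point does not extend to POCD, for which a preoperative 6CIT baseline is planned. Both outcomes are secondary, and the article declares these analyses exploratory. The primary VAS analysis and the planned 327 (360 with dropout) are unaffected. This is a minor point.

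**What to change.** In Neuroinflammatory-Related Complications and Secondary Study Parameters:

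1. Define one index time for all three arms: the start of the first session or, in standard care, the 10:40 slot of the first treatment day.
2. Count as the delirium outcome only new episodes after the index time, among patients free of delirium at that time. Patients with earlier delirium must leave the risk set; otherwise they would be counted as event-free. Report earlier episodes by arm as a baseline characteristic.
3. Run the 24-hour analgesic periods from the same index time. If a pre-session dose is used as a covariate, keep intraoperative drugs out of it, because the preceding 24 hours may include the operation.
4. Report the interval from surgery to the index time by arm, using the postoperative day already recorded. This matters more once the count is anchored, because an arm with a longer interval starts its count later after surgery. The whole-admission count can stay as a supporting result.

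The cost is a wording change, fewer delirium events and a slightly smaller risk set. It also needs DOSS and medication records with dates and times, and the article does not confirm that times are captured. The sample size does not change.

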### Other Parameters

A short, 6-item questionnaire [27,28] will be added to the standard preoperative intake in order to assess preoperative cognitive status, as well as a short questionnaire about the musical background (excerpt from the DMBQ) [29,30]. Both the cognitive status and the musical background will help to interpret the results. The preoperative cognitive status will serve as a baseline for postoperative cognitive status as well as alpha power in EEG recordings. The musical background will be assessed as a possible explanation for the success of the live or recorded music interventions. Other complications (classified according to Clavien-Dindo [33], nursing-sensitive outcomes such as dehydration and falling [34]) will be explored for changes in the music groups compared to care-as-usual to derive hypotheses for future studies.

### Statistical Analysis

The primary outcomes of this study are VAS subject pain ratings. The *F* test is described immediately below. Statistics will be conducted with SPSS (IBM Corp) or equivalent software [36].

### Primary Study Parameters

Pain ratings will be collected 4 times a day with a VAS. VAS mean and SD will be reported, and box plots, histograms as well as *P* values for Kolmogorov-Smirnov tests will be evaluated for normality of distribution. A univariate, one-way repeated measures (RM) ANOVA will be conducted with factors group (live music intervention, recorded music active control, and standard care control) by time points (1, 2, 3, 4). The α significance threshold will be .05. The result of interest is the significance of the training×time point interaction, that is, whether the course of the data across time points was altered by the training type. Data are planned with 4 time points; in case of up to 2 missing time points, data will be interpolated [37]. Cases with more than 2 missing time points will be excluded from the analysis. Alternatively, if the residuals of the ANOVA are not normally distributed, a similar Kruskal-Wallis one-way ANOVA will be conducted.

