## Methods

### Study Design

The study will take place at the University Medical Center Groningen (UMCG), which has already hosted the Meaningful Music in Healthcare (MiMiC) live intervention [25]. The intervention study follows an on-off nonrandomized controlled trial (NCT) design [26]. The NCT is necessary for this particular intervention in practice because the live music intervention cannot easily be randomized to skip patients in the same ward without them hearing the music or seeing the musicians as they play for other patients and nurses.

In this NCT design, treatments and data collection will be conducted in 15 blocks over the course of 4 years. According to the 29-day treatment block, the three 5-day treatments (live music intervention, recorded music active control intervention, and standard care control) will be offered with a 7-day washout between treatments. The washout will minimize the number of participants whose hospital stay overlaps with another treatment. Based on the previous research (UMCG research register 201600541), we expect approximately 8 full data sets per 5-day treatment block.

Note that while the intended outcome of the music intervention is therapeutic (eg, experiencing reduced pain), the music intervention is conducted by conservatory-trained music practitioners but not by music therapists. Music therapists are licensed therapists who have a degree in music therapy including clinical training. The music practitioners in this study are primarily professional musicians who have taken 1 music-conservatory course and several internships to train them for clinical settings but they are not therapists.

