Design procedures are chronologically displayed in Figure 1. Preoperative questionnaires will be collected to assess cognitive function (6-item cognitive assessment [6CIT]) [27,28] and musical background (excerpt from the Dutch Musical Background Questionnaire [DMBQ]) [29,30]. Postoperative data collection procedures per day of treatment include pain visual analog scale (VAS) ratings, heart rate (HR), and blood pressure measuring 4 times a day (before, directly after, 3-hour, and 6-hour postintervention). EEG electrodes will be applied once in the morning and 4 EEG recordings will be collected with VAS ratings, HR, and blood pressure (before, during, 3-hour, and 6-hour postintervention). A blood sample will be collected once daily and integrated with standard care as far as possible (eg, if blood is drawn as part of standard care, the sample will be collected from the same needle). A schedule of assessments may be found in Table 1. Daily dosage of pain medication as well as any incidence of delirium (delirium observation screening scale [DOSS]) [31] or POCD will be collected.

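### Treatment is allocated by whole 5-day periods, but the primary ANOVA and the sample size treat patients as independent, so the nominal .05 error and 0.90 power are not assured

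*Protocol article*

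**What the plan says.** **Allocation.** Study Design states that "treatments and data collection will be conducted in 15 blocks over the course of 4 years". Each 29-day block holds three 5-day treatments, which "will be offered with a 7-day washout between treatments". The yield is given as "we expect approximately 8 full data sets per 5-day treatment block". Treatment Allocation says that the design "allocates participant inclusion by alternation" and that "the patients included will be offered whichever treatment is occurring during their hospital stay". The calendar is fixed months ahead. The unit that receives a treatment is therefore the 5-day period, not the patient.

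**Analysis.** Primary Study Parameters states: "A univariate, one-way repeated measures (RM) ANOVA will be conducted with factors group" (three arms) and four time points. The test of interest is the group×time interaction at .05. No term for treatment week or block is named. Other Study Parameters adds only patient baseline characteristics, post hoc.

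**Sample size.** Power and Table 3 give 327 participants, 3 groups, 4 measurements, denominator df 972 and actual power 0.9008, padded to 360. No allowance is made for allocation by period.

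**The concern.** When whole periods are assigned, patients treated in the same period may resemble each other in ways that have nothing to do with the arm. Sessions take place at a common hour (Table 1), and in live weeks the musicians move around the ward (Treatment Allocation), so patients in one live week share the same performances. Patients in any week share a ward routine. If the within-day pain course varies from week to week, part of the apparent arm difference is a difference between weeks, and the evidence on it comes from 15 weeks per arm, not from 120 patients.

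A test that ignores this rejects too often, and a sample size that ignores it promises too much power. The power figure is also used during the trial: according to Results, preliminary analysis starts once the data reach 0.8 power, and that point is placed using the same independence assumption.

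**Working it through.** **Inputs from the article.** 15 blocks, three 5-day treatments per block, 7-day washouts, about 8 patients per treatment period (Study Design); group×time interaction, α = .05 (Primary Study Parameters); f = 0.2318206, power 0.9, 3 groups, 4 measurements, ε = 1, N = 327, then 360 (Power, Table 3).

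**Structure.** 3×5 + 2×7 = 29 days per block. 15×3 = 45 periods, 15 per arm. 15×8 = 120 per arm; 45×8 = 360.

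**Reproducing Table 3.** λ = f²×N = 0.0537408×327 = 17.573; numerator df (3−1)(4−1) = 6; denominator df (327−3)×3 = 972; critical F 2.1079; power 0.9008. All agree. The arithmetic is right for independent patients.

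**Which week variation matters.** The interaction compares time points within patients. A week effect that is the same at all four ratings drops out: simulating the planned test with 45 weeks of 8 and a constant week variance of 0.10 gave a rejection rate of 0.053. A week×time component does not drop out. If it makes up a share ICC of the time-specific variance, the variance of an arm's within-day profile is multiplied by DE = 1 + (m−1)×ICC, with m patients per week.

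**Type I error of the planned test.** The effective threshold is the critical F multiplied by [(n−DE)/(n−1)]/DE, with n = 120 per arm. At ICC 0.05: DE = 1 + 7×0.05 = 1.35; 2.107×(118.65/119)/1.35 = 1.556; the probability that F on 6 and 1071 df exceeds 1.556 is 0.157. Simulation of the full test gives 0.16.

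**Power of a valid test.** λ = f²×N/DE on week-level df (45−3)×3 = 126. At ICC 0.05 and N = 360: 19.347/1.35 = 14.33, power 0.800. With N = 327, m = 327/45 = 7.27 and DE = 1 + 6.27×0.05 = 1.313: 17.573/1.313 = 13.38, power 0.768.

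The documents give no ICC, so the values below are an assumed range. The last column is 327×DE, ignoring the loss of df.

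| ICC (week×time) | DE, m = 8 | Type I, all arms | Type I, live weeks only | Power, 360 | Power, 327 | N for about 0.90 |
|---|---|---|---|---|---|---|
| 0 | 1.00 | 0.05 | 0.05 | 0.918 | 0.886 | 327 |
| 0.01 | 1.07 | 0.06-0.07 | 0.06 | 0.896 | 0.863 | 350 |
| 0.02 | 1.14 | 0.08-0.09 | 0.06 | 0.873 | 0.839 | 373 |
| 0.05 | 1.35 | 0.16 | 0.08-0.09 | 0.800 | 0.768 | 441 |
| 0.10 | 1.70 | 0.28-0.29 | 0.12-0.13 | 0.685 | 0.658 | 556 |

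Ranges reflect separate simulation runs.

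**Sensitivity to the effect-size scaling.** Table 3 uses λ = f²×N. If the partial η² of 0.051 came from the univariate interaction test (an assumption; the article does not say), the matching λ would be f²×972 = 52.2, and power would stay above 0.99 even at ICC 0.10. The type I error does not depend on this.

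**The case against.** The strongest defence is that the chosen test is partly protected. Differences between weeks in general pain level, case mix or ward practice cancel from the interaction if they are constant over the day. This stands, and it means that an ordinary ICC for pain level is not the relevant quantity.

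Second, shared musicians explain week×time variation in the live arm only; recorded music comes over headphones and standard care has no music. This also stands in part. With variation in live weeks only, the inflation is much smaller (about 0.06 to 0.13). Variation in the other arms would have to come from ward routine or other shared conditions, which the article neither shows nor rules out.

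Third, if all 360 patients contribute, power stays near 0.90 at ICC 0.01. That is correct.

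A reader might also infer two further faults, which the documents do not support:

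- *That up to five days of ratings make p-values too small.* "Pain ratings will be collected 4 times a day with a VAS", on each treatment day, while the model has four time points. But the Power section speaks of four measurements per participant, and averaging days to four values per patient keeps the error nominal (0.047 in simulation). Inflation arises only if patient-days are entered as separate cases (0.19 with 3 days and 0.32 with 5, for an assumed patient×time share of 0.2), which the article does not say. How days are combined is a detail that an article may leave to the analysis plan.
- *That four years of calendar drift enter the error term.* Drift in pain level cancels within patients, and every block contains all three treatments.

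**Conclusion.** The mismatch is in the text: allocation is by 45 periods, while the primary test and its 972 df are those of independent patients, with no week or block term and no design effect. The consequence is conditional. If within-day profiles correlate within weeks, the true type I error exceeds .05: modestly at an ICC of 0.01, about three times nominal at 0.05 in all arms, less if only live weeks vary. On Table 3's own scaling, power with 360 analysed falls from 0.92 at ICC 0 to 0.80 at ICC 0.05, and with 327 analysed it is below 0.90 throughout.

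A reader might conclude that the p-values are too small and that the power is not delivered. The documents do not establish either, because they give no week×time correlation. What can be said is that neither the .05 nor the 0.90 is assured. Since the remedy is cheap and data collection was planned to run until 2026, the analysis should be corrected before the data are examined.

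**What to change.** Replace the primary RM ANOVA with a linear mixed model:

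- Fixed effects: arm, time, arm×time and block (1-15), with arm×time as the primary test.
- Random effects: treatment week, week×time and patient.
- Kenward-Roger or Satterthwaite df, so that the interaction is judged at week level (about 126 df). If block×time is fitted as well, (15−1)×3 = 42 df go, leaving 84, and power with 360 becomes 0.89, 0.86, 0.79 and 0.67 for the four ICC values.
- If all days are used, add treatment day as a fixed effect and random patient-day and patient×time effects, so that patient-days are never treated as independent cases.
- Use the first-day pre-intervention VAS either as a covariate or as an outcome, not both.

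Restate the power with DE = 1 + (m−1)×ICC. Define the ICC as the week-level correlation of the within-day profile, and show a range such as 0.01 to 0.05. Base the 0.8-power trigger for preliminary analysis on the same calculation.

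Cost: a change of wording and model, which SPSS can fit, and no new data. Confidence intervals become somewhat wider and the stated power less favourable.

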#### Power

The sample size was calculated using G*Power 3.1 [38], an industry-standard software. Below, we explain the parameters for an RM between-subjects univariate ANOVA as well as the final sample size. The calculation was based on the desired ability to detect a within-between interaction (intervention group×time point), with recommended internal settings from [39], which would effectively indicate whether the live music intervention altered the slope of outcome measurements compared to the recorded music or do-nothing control groups.

The effect size (partial η^2^=0.051, converted to f=0.2318206) was determined from a retrospective RM ANOVA with published data [1].

Alpha: As we have a single quantitative outcome measure, alpha may remain at the conventional .05 significance threshold.Power: Following recent recommendations to set power above the typical 0.8 to 0.9 and higher [40], the threshold was set at 0.9.Number of groups or measurements: The design calls for 3 groups, with 4 RM (see “Study Design” section; before treatment, after treatment, 3-hour, and 6-hour follow-up) for each participant.Nonsphericity correction: As mentioned earlier, retrospective analyses were conducted with the data published in [1]. The ANOVA conducted with that data passed the assumption of sphericity (*P*=.07); therefore, no correction (1) was entered in the G*Power calculation.Sample size: The sample size (n=327, Table 3) outputted from G*Power represents the total number of participants in a 3-group design required to achieve 0.9 power with an effect size of ~0.232-109 per group. Padding for a 10% dropout rate raises the per group n to 120, for a total N of 360.

**Table 3 table3:** G*Power sample size calculation.

Parameters			Value

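### Treatment is allocated by whole 5-day periods, but the primary F test and the power calculation count patients as independent; alpha .05 and power 0.9 hold only if patients in a period share no within-day pain course

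*Protocol article*

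**What the plan says.** **Allocation** (Protocol article, Study Design and Treatment Allocation). The schedule is fixed months ahead, and "the patients included will be offered whichever treatment is occurring during their hospital stay". As to scale, "treatments and data collection will be conducted in 15 blocks over the course of 4 years", each block holding one 5-day period of each of the three treatments, and "we expect approximately 8 full data sets per 5-day treatment block".

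**Primary analysis** (Primary Study Parameters). "A univariate, one-way repeated measures (RM) ANOVA will be conducted with factors group" and four time points. "The result of interest is the significance of the training×time point interaction". "The α significance threshold will be .05". Neither block nor treatment period enters the model. The extra covariates and factors under Other Study Parameters are baseline parameters such as age and type of surgery.

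**Sample size** (Power and Table 3). For power, "the threshold was set at 0.9". The G*Power result of 327 "represents the total number of participants in a 3-group design required to achieve 0.9 power", with 6 and 972 df and no ICC or design effect. It is padded to 360. Clustering by period is not mentioned under Limitations either.

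**The concern.** The unit that receives a treatment is the period, not the patient. Patients in one period share a calendar week and, in live weeks, the musicians and their sessions. The session falls between the first and second ratings of the day (Table 1), so anything about it that is common to a period can alter the pain course from rating 1 to ratings 2, 3 and 4. That course is what the group × time interaction tests.

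If such sharing exists, the patient-level error term is too small. The test then rejects a true null hypothesis more often than 5% of the time, and a test with the right error term has less power than stated. This is the confirmatory test and the only power statement in the plan, and the Conclusions say that the result may inform policy makers.

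**Working it through.** **Inputs from the protocol.** 15 blocks × 3 treatments = 45 periods, 15 per arm. About 8 patients per period gives 15 × 8 = 120 per arm, which is the planned N of 360. Partial η² = 0.051, 3 groups, 4 measures, α = .05, ε = 1.

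**Assumed.** The period × time ICC: the share of the within-patient residual variance that is common to patients in the same period at the same time point. The documents give no value, so the range .01 to .10 is used.

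**1. The plan's own figure**
- f² = 0.051/0.949 = 0.05374, so f = 0.2318.
- λ = f² × 327 = 17.573.
- df1 = (3−1)(4−1) = 6 and df2 = (327−3)(4−1) = 972.
- Critical F = 2.1079 and power = 0.9008.

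Table 3 reproduces. The 972 df show that each of the 327 patients is counted as an independent unit.

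**2. Which clustering matters.** A period effect that is equal at all four ratings drops out of a group × time contrast. In simulation (15 periods of 8 per arm) with period-level variance of 0.1 and no period × time variance, the planned test rejected in about .05 of null trials. Only the period × time component does harm here.

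**3. Type I error of the planned test.** The design effect is DE = 1 + (8−1) × ICC. A close approximation is P(F(6, 972) > 2.1079/DE). Simulated values are from 20,000 null trials per cell, with 15 periods of 8 per arm.

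| ICC | DE | Approximation | Simulated, all arms | Simulated, live arm only |
|---|---|---|---|---|
| .01 | 1.07 | .067 | .07 | .06 |
| .02 | 1.14 | .087 | .09 | .06 |
| .05 | 1.35 | .155 | .16 | .08 |
| .10 | 1.70 | .283 | .29 | .11 to .12 |

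Independent runs of the all-arms case gave .08 to .10 at ICC .02 and .15 to .16 at ICC .05. An F test on the 45 period means with block as a factor stayed at about .05 throughout.

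**4. Power of a period-level test with block.** The error df are (15−1)(3−1)(4−1) = 84 and the critical F is 2.209. The noncentrality is λ = f² × N/DE, with 327/45 = 7.27 patients per period at N=327 and 8 at N=360. No credit is taken for variance that block may remove.

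| ICC | Power, N=327 | Power, N=360 |
|---|---|---|
| 0 | .88 | .91 |
| .01 | .85 | .89 |
| .02 | .83 | .86 |
| .05 | .76 | .79 |
| .10 | .65 | .67 |

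Example, ICC .05 at N=327: DE = 1 + 6.27 × .05 = 1.313, λ = 17.573/1.313 = 13.38, power = .756.

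The N=360 column assumes that nobody drops out. The loss from .90 to .88 at ICC 0 comes from having fewer error df, not from clustering.

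**The case against.** **A week effect cancels.** Shared staff, surgical lists and season most naturally shift the level of pain, and a constant shift drops out of the interaction. This stands. A reader might infer that any good or bad week can pass for a treatment effect in the primary test. It can do so only if it changes the course over the four ratings.

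**No ICC is shown.** This stands too. A reader might infer that alpha and power have been shown to fail. The documents support only that both rest on an unstated assumption of zero period × time correlation. The 29% is the top of an assumed range, not an estimate.

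**Clustering may differ by arm.** Shared musicians exist only in live weeks. Recorded music is preselected and heard over headphones, and controls receive no music. If the ICC exists in the live arm alone, the inflation is much smaller (.06 to about .12). Nor does the protocol establish that all patients in a period lie on one ward, since all surgery types are eligible.

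**Padding to 360 covers it.** Only in part. At ICC .01 with no dropout, power returns to .89, but the type I error of the planned test stays at about .07. More patients in the same 45 periods enlarge the design effect.

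**A nonrandomized period design is justified.** This is not disputed. The point concerns how the data from that design are analysed.

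**Conclusion.** Wrong as written. The stated model and power figure do not match the stated allocation, and this does not depend on any ICC: 45 allocated units are analysed as 327 to 360 independent ones. How much it matters does depend on the period × time ICC. At zero, the planned test is valid. At .01 to .10 in all arms, the nominal 5% becomes about 7% to 29%, and the power of a valid test with block falls from .88 to between .85 and .65 at N=327. These are sensitivity values that rest on about 8 patients per period, equal period sizes and the protocol's own effect size.

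Two further readings go too far. One is that 0.90 at N=327 would be right for a period-level test if the ICC were zero; that test reaches .88. The other is that every secondary F test is declared the same as the primary. That is said only of the EEG and physiological measures. Blood markers get a two-point RM ANOVA. Delirium and postoperative cognitive decline get a patient-level one-way test, and there even a constant period effect does not cancel.

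**What to change.** - **Primary Study Parameters.** Replace the RM ANOVA by a linear mixed model with fixed group × time point and block × time point, random patient, treatment period and treatment period × time point, and Kenward-Roger or Satterthwaite df. A group × time ANOVA on the 45 period means with block as a factor is a close alternative. It is equivalent only with equal period sizes and complete data.
- **Secondary Study Parameters.** Use a period-level error term for the EEG, physiological and blood-marker analyses, and for delirium and postoperative cognitive decline.
- **Power.** State that 0.90 at N=327 assumes independent patients. Tabulate the power of the period-level test over a stated ICC range at N=327 and N=360.
- **Data.** Make sure that block and treatment period are recorded for each patient. Both follow from the dates of stay and the schedule.

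The cost is revised analysis wording and a less favourable stated power, with wider intervals in the results. No extra patients or data are needed. Only 5 participants had been recruited at submission, so the change can be made well before the results are known.
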